##### Wong-Baker Faces Pain Rating Scale

The WBS is a widely used self-reported tool to assess pain using a series of six facial expressions to illustrate the degree of pain [40]. A numerical value is assigned to each face, from 0 (no hurt) to 10 (hurts worst); thus, each face equates 2 points. It has been validated among children above the age of 3 with sickle cell anaemia and human immunodeficiency virus (HIV) infection as well as children undergoing venepuncture and minor surgery [42]. The WBS has an MCID of one face (2 points) [43].

### Explorative outcomes

#### Radiographs

The remodelling process will be evaluated by the axial alignment of radius on antero-posterior (AP) and lateral radiographs taken at 6 and 12 months. Angular malalignment in metaphyseal and physeal fractures is determined as the angle formed by the intersection of two lines parallel to the axis of the radius proximal and distal to the fracture site or growth plate. Physeal arrest will be recognized by the presence of focal bone density bridging across the normally lucent physis.

### Photographs

We will take photographs (AP and lateral views) at the time of injury, 4 weeks, and 3-, 6-, and 12-month visits to observe the cosmetic progress.

No systematic measurements will be made on radiographs or photographs, but they may support our primary and secondary outcomes and used for didactic purposes.

### Participant timeline

We will follow the Standard Protocol Items Recommendations for Interventional Trials (SPIRIT) (Table 1).

**Table 1 Tab1:**
[figure not shown]
Standard Protocol Items Recommendations for Interventional Trials (SPIRIT) diagram. QuickDASH, Quick Disabilities of the Arm, Shoulder and Hand. EQ-5D-Y, EuroQol Youth version to measure Health-Related Quality of Life (HRQoL). WBS, Wong-Baker Faces Pain Rating Scale

### Sample size

We defined a non-inferiority margin as NIM = MCID = 15 QuickDASH points. Thereby, we will only reject the null-hypothesis, if the between-group difference is *both* more than NIM *and* clinically relevant. With an SD = 15 and type I error rate of 2.5%, 16 patients per group (32 in total) would be required for 80% power that the lower limit of a 95% two-sided confidence interval (CI) would be above the non-inferiority limit [44]. Allowing for 20% dropouts, the total sample size required is 40 patients (20 in each group).

### Recruitment

We will have four recruiting centres, thereby improving the rate of enrolment.

## Assignment of allocation

### Sequence generation

A person not otherwise involved in the study will generate a random allocation sequence in the R software with block randomization (70 blocks with shifting block sizes of 2, 4, and 6 in each block). The same person with no other user rights will upload the table in the software Research Electronic Data Capture (REDCap), and the table will be blinded to all other investigators.

### Concealment of allocation

The local investigator, with randomization rights assigned by the principal investigator (PI), will log into REDCap and irreversibly allocate patients into one of the two treatment groups. The local investigator is responsible for providing the allocated treatment by either scheduling the patient for surgery or applying a cast (or leaving the already applied cast).

## Blinding

It is not possible to blind the surgeon, the patient, or the parents/guardians to the treatment allocation. PROM scores and 6- and 12-month radiographs will be evaluated by persons blinded to treatment allocation and not otherwise involved in the study. Data analysis will be performed by an external biostatistician blinded to treatment allocation.

### Patient and public involvement

Three parents read and commented on the written information sheet, thereby reassuring that it was understandable and sufficiently informing.

## Data collection and management

### Data collection

We will collect baseline data and outcome measures by 4 weeks and 3, 6, and 12 months post-injury in REDCap (or paper forms if no REDCap access) (Additional file 2). Link to questionnaires will be sent by email 2 days prior to the appointment.

### Participant retention

Efforts will be made to inform patients of the importance of completing the entire study period. By receiving questionnaires electronically 2 days in advance, patients will be reminded of their appointment.

Patients may withdraw from the study for any reason at any time. Patients will be excluded from the trial if they fail to show up despite two phone call reminders. We will include data obtained until withdrawal in the statistical analysis.

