### Primary outcome measure

The primary outcome will be the PROM, Quick Disabilities of Arm, Shoulder and Hand (QuickDASH) [26], at 12 months. This 11-item questionnaire is a shortened version of the 30-item Disabilities of the Arm, Shoulder and Hand (DASH) [27]. The DASH was designed to help report the disability experienced by adults with upper-limb disorders covering different activities of daily living, and also monitoring changes over time.

The QuickDASH has, like the DASH, two four-item optional modules, work and sports/performing artists, which are scored separately. The QuickDASH and the DASH have comparable psychometric properties [28].

The patient rates each item (with help by parents if the patient is too young to self-report) according to the perceived degree of severity using a 5-point Likert scale. The overall score is transformed to a score between 0 and 100 (0 = no disability, 100 = maximum disability).

Although the QuickDASH was developed on adults, it has been used in several studies on children with different upper extremity fractures. Unfortunately, these studies report only total QuickDASH scores (mean (standard deviation (SD))) and *p*-values but do not take into account the clinical relevance of the differences [29–33].

We have identified four studies using anchor-based approach to determine the minimal clinically important difference (MCID) in adults [34–37]. Mintken et al. [37] reported an MCID of 8 on 101 adults with shoulder pain. Sorensen et al. [35] reported an MCID of 14 on 48 adults with non-operatively treated atraumatic hand and forearm conditions. Franchignoni et al. [34] reported an MCID of 15.9 on 266 adults with upper-limb musculoskeletal disorders, referred to inpatient and outpatient physiotherapy. In a similar population, Polson et al. [36] reported an MCID of 19 on 35 adults with musculoskeletal conditions to the upper extremity, referred to physiotherapy. We derive an MCID of 15 from the reported MCIDs, and since no MCID is reported in children’s cohorts, we assume it to be roughly comparable to adults.

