### Primary outcome analysis

The primary endpoints will be reported as mean QuickDASH scores on a continuous scale between 0 and 100 and will be analysed by the per-protocol (PP) population and repeated, for sensitivity reasons, for the intention-to-treat (ITT) population. Non-inferiority will be concluded only if both PP and ITT analyses show non-inferiority.

The between-group difference in mean QuickDASH score by 12 months will be compared using linear mixed effects models (LMM).

Non-inferiority will be concluded if the lower end of the 95% CI is above the NIM of 15 QuickDASH points.

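### A missed visit ends trial participation, so the emailed 12-month QuickDASH is no longer sought from children who could still supply it

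*Protocol article*

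**What the plan says.** The rule stands in the protocol article under Participant retention: "Patients will be excluded from the trial if they fail to show up despite two phone call reminders". It names no visit, and Outcomes schedules follow-up at 4 weeks and at 3, 6 and 12 months. The same paragraph goes on: "We will include data obtained until withdrawal in the statistical analysis".

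The endpoint is given under Primary outcome measure: "The primary outcome will be the PROM, Quick Disabilities of Arm, Shoulder and Hand (QuickDASH) [26], at 12 months". The child answers the questionnaire, with parental help if too young. On delivery, Data collection says: "Link to questionnaires will be sent by email 2 days prior to the appointment". Answers go into REDCap, with paper as a back-up. Nothing in the article describes collecting questionnaires from a child after a missed visit.

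Three further places bear on the consequence:
- Primary outcome analysis uses the per-protocol population, "repeated, for sensitivity reasons, for the intention-to-treat (ITT) population", and requires non-inferiority in both.
- Handling of missing data addresses wholly missing questionnaires by a linear mixed model, assuming dropout is missing at random.
- Sample size allows 20% dropout, which takes 32 evaluable children to 40 randomised.

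**The concern.** The rule makes attendance a condition for staying in the trial, but the primary outcome does not depend on attendance. Nor do the secondary outcomes: QuickDASH at 3 and 6 months, EQ-5D-Y and the Wong-Baker scale are all patient-reported. The radiographs and photographs do need a visit, but they are explorative and the article plans no systematic measurements on them.

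A family that misses an early visit may still be willing to answer an email at 12 months. Under the rule as written, nobody asks them.

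Two things are at stake. The first is bias. Families know their allocation, so who stops attending may depend on how the arm is doing or on how satisfied the family is. Families of recovered children may see no reason to come, and dissatisfied families may go elsewhere. The second is precision. With 16 evaluable children needed per arm, each one is 1/16, or about 6%, of an arm.

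**Working it through.** **1. When the rule costs primary-outcome data**

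- Missed visit at 4 weeks, 3 months or 6 months: the child is excluded before month 12, so the 12-month QuickDASH is not sought. This is the clear loss.
- Missed visit at 12 months: the link went out two days earlier. A form already returned is arguably data obtained before exit and is kept. A form not yet returned is lost if nobody follows it up.

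**2. What the mixed model has to work with**

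A child who misses the 3- or 6-month visit may already have returned that questionnaire, and any earlier ones, by email. The model can use those scores, but only under missing at random. For a child excluded at 4 weeks, Secondary outcome measures lists QuickDASH from 3 months only, whereas Data collection speaks of outcome measures from 4 weeks. The schedule in Table 1 is not shown in the text at hand, so whether such a child has any score cannot be settled.

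**3. Reproducing the planned size**

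Inputs from Sample size: margin 15, SD 15, one-sided type I error 2.5%, power 80%, true difference taken as 0.

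n per arm = 2 × (1.960 + 0.842)² × 15² / 15² = 15.7, rounded up to 16; total 32. With 20% dropout, 32 / (1 − 0.20) = 40. The stated figures reproduce.

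**4. Power by number evaluable per arm, SD 15**

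SE = 15 × √(2/n); non-centrality = 15 / SE; degrees of freedom 2n − 2; one-sided 2.5%.

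| n per arm | SE | Non-centrality | Power (normal) | Power (t) |
|---|---|---|---|---|
| 16 | 5.30 | 2.83 | 80.7% | 78.1% |
| 18 | 5.00 | 3.00 | 85.1% | 83.0% |
| 20 | 4.74 | 3.16 | 88.5% | 86.9% |

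The allowance is 40 − 32 = 8 children. The row for 20 assumes that all 8 are non-attenders and that all are recovered; the row for 18 assumes half. The documents give no such share, so the last row is a ceiling.

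**5. Dependence on the SD**

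Primary outcome measure cites SDs of 11.6 and 16.4 at about 3 months. The same t-based calculation gives:

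| SD | Non-centrality, 16 / 20 per arm | Power, 16 per arm | Power, 20 per arm |
|---|---|---|---|
| 11.6 | 3.66 / 4.09 | 94% | 98% |
| 16.4 | 2.59 / 2.89 | 71% | 80% |

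**6. Illustration of the bias**

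Suppose a share f of one arm is not measured and its 12-month mean differs by D points from that of the children retained. The complete-case mean of that arm is then off by f × D. For f from 0.1 to 0.3 and D from 5 to 20, both assumptions that are not in the documents, the shift runs from 0.1 × 5 = 0.5 to 0.3 × 20 = 6 points, against a margin of 15. A mixed model may reduce this where earlier scores explain the difference. The direction is unknown: losing dissatisfied families from the casting arm favours non-inferiority, and losing recovered children from that arm works against it.

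**The case against.** The case on the other side is substantial on the consequences, less so on the rule.

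- **Data are kept.** A reader might infer that the rule throws away scores. It does not: the sentence after it retains what was obtained until exit. The fault is that collection stops.
- **The mixed model may still use the child.** A reader might infer that a child excluded at 4 weeks or 3 months has no QuickDASH and is beyond the model's reach. The article does not establish this. A 3-month form can be returned by email before the visit is missed, and the 4-week schedule cannot be checked.
- **Intention-to-treat is not contradicted.** A reader might infer that exclusion from the trial means removal from that population. Nothing says so. The rule weakens the analysis through missing values.
- **Power is already budgeted.** The plan allows for 16 evaluable per arm, and by its own formula that gives 80.7%. The 78.1% comes from using the t distribution, which is a separate matter from retention. The allowance must also cover cross-overs to surgery, which the article counts as drop-outs, and voluntary withdrawals. Families who have ignored two calls will not all answer a third approach.
- **The bias is plausible, not shown.** The documents give neither evidence nor size for it.

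All five stand as limits on the claim. None supplies a reason to stop asking for an emailed questionnaire after a missed visit.

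**Conclusion.** The point holds as a recommended change. Followed as written, the rule creates avoidable missing 12-month QuickDASH scores, mainly among children who miss an earlier visit. It leaves them to a missing-at-random assumption that is open to doubt when families know the treatment. It thereby weakens the intention-to-treat result on which the non-inferiority conclusion also depends.

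The main reason to act is bias, which the 20% allowance does nothing to prevent and whose size the documents do not allow anyone to estimate. The power gain is secondary and bounded: at SD 15, somewhere between nothing and about 9 percentage points (86.9% − 78.1% = 8.8), depending on how many of the 8 budgeted losses are non-attenders who can be reached. At SD 11.6 the ceiling is about 4 points, and at SD 16.4 about 10.

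That the rule covers every visit is certain from its wording. That later questionnaires are not sought is inferred from exclusion from the trial, together with the absence of any provision for collecting them.

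**What to change.** Replace the exclusion sentence under Participant retention with wording such as:

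*A missed visit ends neither participation nor questionnaire collection. The link is re-sent, and all later questionnaires, including the 12-month QuickDASH, are sought by email or phone unless consent to data collection is withdrawn. All randomised children remain in the ITT population.*

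Keep the existing sentence on data obtained until withdrawal for families who do withdraw consent. The change leaves treatment, eligibility, visit schedule and sample size as they are. It costs one amended sentence and a few extra emails and calls. Recruitment is expected to finish in May 2025, so 12-month follow-up of the last children runs to about May 2026. A change made before follow-up ends can still secure primary-outcome data.

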### Data management

Approval from the Data Protection Agency of Region Zealand have been obtained (REG-099–2022) before trial commencement. Compliance with the General Data Protection Regulation (GDPR) and the Danish Data Protection Act will be ensured at all times. A data processing agreement has been signed with all recruiting centres. All completed paper forms will be stored in locked file cabinets with limited access before and after they are entered in REDCap (with two-factor authentication login). The REDCap setup ensures that randomization is only possible, if all baseline information is entered correctly. Other electronic participant information, if any, will be stored on a secured study-specific drive owned/managed by the PI. All data will be fully anonymized before publication.

## Statistical methods

Data analysis will be conducted by an external biostatistician. Descriptive statistics will be used to report demographic data.

Continuous variables will be reported by mean with SDs or median with interquartile range (IQR), depending on the distribution, and compared using *t*-test for normal distributed variables and Mann–Whitney *U* test for non-normal distributed variables. Categorical variables will be reported by numbers and percentage and will be compared using Pearson’s chi-square test.

Significance is set as *p*-value < 0.05.

### Primary outcome analysis

The primary endpoints will be reported as mean QuickDASH scores on a continuous scale between 0 and 100 and will be analysed by the per-protocol (PP) population and repeated, for sensitivity reasons, for the intention-to-treat (ITT) population. Non-inferiority will be concluded only if both PP and ITT analyses show non-inferiority.

The between-group difference in mean QuickDASH score by 12 months will be compared using linear mixed effects models (LMM).

Non-inferiority will be concluded if the lower end of the 95% CI is above the NIM of 15 QuickDASH points.

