**Methods:**

A multicentre non-inferiority randomized controlled trial. Children aged 4–10 years with a displaced distal forearm fracture will be offered inclusion, if the on-duty orthopaedic surgeon finds indication for surgical intervention. They will be allocated equally to non-surgical treatment (intervention) or surgical treatment of surgeon’s choice (comparator). Follow-up will be 4 weeks and 3, 6, and 12 months. The primary outcome is the between-group difference in 12 months QuickDASH score. We will need a sample of 40 patients to show a 15-point difference with 80% power.

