### Trial design

A pragmatic, randomized, controlled non-inferiority multicentre trial with two parallel groups allocated 1:1 by block randomization. Primary outcome is patient-reported function after 1 year.

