## Interventions

A cast will be applied in the emergency room as standard procedure. Children will be randomly allocated 1:1 to:Non-surgical treatment (intervention): No reduction. Cast optimization if necessarySurgical treatment (comparator): Reduction under general anaesthesia with or without pin fixation of surgeons’ choice followed by cast immobilization

The cast will be removed after 4 weeks if radiological signs of healing (callus formation or bone bridges). The casting will be prolonged another 2 weeks if uncertainty of healing. If the initial cast was an above elbow cast, it will be changed to a below elbow cast at this point.

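### The primary decision rule is not a non-inferiority test: on a scale where higher is worse, it asks for a lower 95% limit above 15 and fixes no direction of subtraction

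*Protocol article*

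**What the plan says.** The trial is described under Trial design as "A pragmatic, randomized, controlled non-inferiority multicentre trial with two parallel groups allocated 1:1 by block randomization". The experimental arm is casting ("Non-surgical treatment (intervention): No reduction") and the comparator is surgical reduction. The primary outcome is QuickDASH at 12 months, scored so that a higher value is worse: "0 = no disability, 100 = maximum disability" (Primary outcome measure).

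The margin is unsigned: "We defined a non-inferiority margin as NIM = MCID = 15 QuickDASH points" (Sample size).

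The decision rule appears under Primary outcome analysis: "Non-inferiority will be concluded if the lower end of the 95% CI is above the NIM of 15 QuickDASH points". Both the per-protocol and the intention-to-treat analyses must meet it.

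Three other statements bear on the rule:

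- Sample size, on the hypothesis: "Thereby, we will only reject the null-hypothesis, if the between-group difference is". The sentence goes on to require that the difference exceed the margin and also be clinically relevant.
- Sample size, on the confidence interval: power is the chance that "the lower limit of a 95% two-sided confidence interval (CI) would be above the non-inferiority limit". No sign is given for that limit.
- Abstract, Methods: "We will need a sample of 40 patients to show a 15-point difference with 80% power".

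No section says which arm is subtracted from which.

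**The concern.** A non-inferiority conclusion requires the data to rule out a deficit as large as the margin. With disability scored upwards, that can be written in two equivalent ways:

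- non-surgical minus surgical: the upper limit lies below +15;
- surgical minus non-surgical: the lower limit lies above −15.

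The written rule is neither. It pairs the lower limit with 15, without a minus sign. The hypothesis sentence under Sample size has the same fault: it rejects the null when the difference is larger than the margin, whereas a non-inferiority null is rejected when the difference is shown to be smaller.

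This is the trial's only confirmatory rule, and both analysis populations depend on it. The analysis is assigned to an external biostatistician blinded to allocation, who needs the direction of the contrast in writing. If sign and direction are settled only after the data are seen, the primary conclusion is open to the charge that they were chosen post hoc.

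**Working it through.** **Inputs.** Margin 15, SD 15, one-sided type I error 2.5%, power 80%, 16 per group, 20% dropout (all from Sample size). The true difference behind the calculation is not stated; I take it as 0, which reproduces the stated number.

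**Reproducing the plan's sample size.**

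- n per group = 2 × SD² × (1.960 + 0.842)² / margin² = 2 × 15² × 2.802² / 15² = 15.7, rounded up to 16, so 32 in total.
- Dropout: 32 / (1 − 0.20) = 40.

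Both figures match. The trial was therefore sized for an ordinary non-inferiority test with the true difference at 0 and the margin 15 points away.

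**Precision at 16 per group.**

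- SE = 15 × √(2/16) = 5.30.
- Half-width of the 95% CI: 1.960 × 5.30 = 10.4 (normal), or 2.042 × 5.30 = 10.8 (t, 30 df).

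**What each rule requires of the observed difference.**

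- Written rule (lower limit > 15): above 15 + 10.4 = 25.4 points (normal) or 15 + 10.8 = 25.8 (t).
- Intended rule, non-surgical minus surgical (upper limit < 15): below 15 − 10.4 = 4.6 points (normal) or 15 − 10.8 = 4.2 (t).

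**Chance of meeting each rule.** For true difference d, with Φ the normal distribution function:

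- written: 1 − Φ((15 − d)/SE + 1.960)
- intended: Φ((15 − d)/SE − 1.960)

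At d = 0, 15/5.30 = 2.83. The written rule gives 1 − Φ(4.79) and the intended rule gives Φ(0.87). The t figures use the non-central t with 30 df.

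| True difference, non-surgical minus surgical | Written rule, normal (t) | Intended rule, normal (t) |
|---|---|---|
| 0 | 8 × 10⁻⁷ (1.3 × 10⁻⁶) | 80.7% (78.1%) |
| 15 (casting worse by the margin) | 2.5% (2.5%) | 2.5% (2.5%) |
| 30 (casting worse by twice the margin) | 80.7% (78.1%) | 8 × 10⁻⁷ (1.3 × 10⁻⁶) |

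**The other subtraction.** For surgical minus non-surgical, the written-rule column is the same with d read as casting's advantage. With equal treatments the rule is met about once in a million trials. Reaching 80.7% (t: 78.1%) needs a true advantage of 30 points for casting.

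**The case against.** The strongest reply is that the authors surely meant surgical minus non-surgical with a limit of −15. On that reading the confidence-interval sentence under Sample size is correct as it stands, the sample size agrees with it, and the rule under Primary outcome analysis has only lost a minus sign. This is probably what was intended, and part of it stands:

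- The confidence-interval sentence under Sample size is incomplete rather than inverted.
- The harmful error, calling inferiority non-inferiority, arises only for non-surgical minus surgical. Under the other subtraction, any result that met the written rule would also be truly non-inferior; the rule is then far too strict, not misleading.
- The 30-point scenario is an illustration at twice the margin, not an assumption of the plan.
- The abstract's phrase is loose shorthand in a text that calls the trial non-inferiority, so changing it is editorial.

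The reply does not rescue the rule. The article gives neither the minus sign nor the direction, so a reader has to supply both. The hypothesis sentence under Sample size repeats the fault, so this is more than one lost character. Nor is it a detail left to an analysis plan: the article states a rule, and the rule it states is wrong.

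**Conclusion.** The concern holds and must be fixed. Under either order of subtraction the stated rule is not a non-inferiority test: it shows casting to be worse by more than 15 points, or it demands that casting be better by more than 15. With equal treatments it would be met about once in a million trials, against the planned 80%. It also contradicts the trial's own sample size, which fits the ordinary test. These figures rest on the plan's SD of 15, on 16 evaluable patients per group, on a simple two-group comparison of means in place of the mixed model, and on an assumed true difference of 0 for the plan's power. The defect itself depends on none of them; it follows from the direction of the scale and the wording of the rule.

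**What to change.** Under Primary outcome analysis, replace the rule with: *The difference is mean 12-month QuickDASH, non-surgical minus surgical (positive values mean non-surgical is worse). H0: difference ≥ 15; H1: difference < 15. Non-inferiority is concluded if the upper limit of the two-sided 95% CI is below +15.*

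Then align the rest:

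- Sample size: rewrite the hypothesis sentence so that the null is rejected when a deficit of 15 points or more is excluded, and restate the confidence-interval sentence with the same direction and sign.
- Abstract (editorial): say that 40 patients (32 evaluable) give 80% power to exclude a 15-point deficit. The 80% is the normal-approximation figure; the t calculation gives 78%.
- Secondary outcome analysis: QuickDASH at 3 and 6 months is to be compared in the same way as the primary outcome, so state whether the non-inferiority rule applies there.
- Carry the wording into the analysis plan and the registry entry if they repeat it; neither was available to check.

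The cost is wording only. Design, margin and sample size (16 per group, 32 evaluable, 40 randomized) are unchanged. The correction should be dated before the primary analysis.
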